## Abstract

**Background:**

Colorectal cancer is the second leading cause of cancer deaths in the UK. Screening is key to early detection. The Scottish programme of colorectal cancer screening is running successfully, and involves all adults aged between 50 and 74 years being invited to post back a faecal sample for testing every 2 years. However, screening uptake is sub-optimal: for example rates for the period November 2009 to October 2011 ranged from just 39% for males living in the most deprived areas to 67% for least deprived females. Recent research has shown that asking people to consider the emotional consequences of not participating in screening (anticipated regret) can lead to a significant increase in screening uptake.

**Methods/Design:**

We will test a simple anticipated regret manipulation, in a large randomised controlled trial with 60,000 members of the general public. They will be randomly allocated to one of 3 arms, no questionnaire, control questionnaire or anticipated regret questionnaire. The primary outcome will be screening test kit return. Results will also be examined by demographic variables (age, gender, deprivation) as these are currently related to screening kit return.

**Discussion:**

If this anticipated regret intervention leads to a significant increase in colorectal cancer screening kit returns, this would represent a rare example of a theoretically-driven, simple intervention that could result in earlier detection of colorectal cancer and many more lives saved.

**Trial registration:**

Current Controlled trials: ISRCTN74986452

## Background

### The problem

Scotland has one of the highest incidences of colorectal cancer (CRC) in the world (43.6 per 100,000 in men, 28.4 per 100,000 in women) and, as in many Western countries, the disease represents the second most common cause of cancer death [1]. Screening is the key to early detection. However, colorectal screening participation varies considerably across countries, and is rarely above 60% [2]. There is also a marked social gradient in participation, with higher social classes often showing double the participation of lower social classes. The importance of this social gradient is further highlighted by the fact that poorer survival following the diagnosis of colorectal cancer is associated with lower socioeconomic status (SES) [2].

A national programme of CRC screening using a guaiac faecal occult blood test (FOBT) is now underway across Scotland [3]. This programme is running successfully and involves all adults aged 50–74 being invited to take their own faecal sample and return it by post for testing every 2 years. The clear social gradient is also strikingly apparent in Scotland, with response rates from low SES groups (particularly males) currently well below 50% [3]. A meta-analysis of screening using FOBT showed a 23% reduction in CRC mortality in participants [4]. Similarly, a recent matched cohort study in Scotland found that screening led to a reduction in overall colorectal cancer mortality by 10%, and in the population that participated, this increased to 27% [5]. Thus the potential benefit of the FOBT screening test clearly depends on the level of uptake, and increasing this is a priority.

### Theoretical background

Although there is recognition that screening uptake rates are low, little work has attempted to identify the key factors which could maximise uptake. This research addresses this gap by drawing on contemporary psychological theories which help explain human behaviour. While many people may approve of FOBT in principle, they may not return their own test kit. The gap between *intention* (e.g. wanting or expecting to use FOBT in the future) and *behaviour* (i.e. actually returning the FOBT test pack) can best be understood by employing a dual-process model in which human behaviour is shaped by two systems. The first is a reflective, rational, goal-oriented system driven by our values and intentions. It requires cognitive capacity, and most traditional approaches to health promotion depend on engaging this system [6]. Often based on providing information, these approaches are designed to educate and alter beliefs and attitudes and motivate people via the prospect of future benefits. At best, these approaches have a modest effect on changing behaviour. The second is an automatic, affective system that requires little or no cognitive engagement, and is more driven by immediate feelings and emotions [6]. Recent work has suggested that health self-care decisions are often not primarily a consequence of rational evaluation of evidence, but may be more directly influenced by emotional/visceral affective beliefs and attitudes (“gut feelings”). In this project we will test whether activating the emotion of anticipated regret leads to a significant increase in FOBT screening uptake.

#### ***Anticipated regret (AR)***

Regret is a negative cognitive-based emotion that is experienced when we imagine that the present situation could have been better had we acted differently. It is also possible to *anticipate* regret and thus act to, or prepare to, avoid actually experiencing this unpleasant emotion. It has been shown that over and above the traditional attitudinal components of influential social cognitive theories such as the Theory of Planned Behaviour (TPB), anticipated regret (AR) adds significantly to the prediction of intentions and prospective health behaviours [7]. To take an illustrative example from the screening literature, Sandberg and Conner [8] invited three groups of women for cervical screening: a control group, a group sent a TPB questionnaire and a group who were asked to complete a TPB questionnaire, and also answer two AR questions on a Likert-style 7 point scale; “If I did not attend for a cervical smear in the next few weeks I would feel regret”, and “If I did not attend for a cervical smear in the next few weeks, I would later wish I had”. In the intention to treat (ITT) analysis (which included those who did not return the questionnaire), screening attendance was 21%, 26% and 26% respectively (i.e. simply sending out a questionnaire increased attendance by 5%). For those who completed and returned the questionnaire (i.e. were definitely exposed to the intervention) attendance rates were 21%, 44% and 65% respectively. This is a quite remarkable effect, given the simplicity, low cost and low intensity of the intervention.

The research to date indicates that subtle AR interventions can significantly increase the likelihood of intention being translated into behaviour, e.g. increasing screening uptake, condom use, exercise, and weight loss [9]. Subtly increasing the prominence of AR in the decision-making process emphasises the aversive emotional consequences of not taking action, and the desire to avoid the aversive feeling of regret then motivates people to translate their positive intentions into action. Essentially, AR strengthens behavioural intentions and binds the person to action, because failing to act is associated with aversive emotions. The present study aims to determine whether a simple AR intervention significantly increases FOBT screening uptake.

#### ***Mere measurement effect***

There is also growing evidence for behavioural change induced by simply completing a relevant questionnaire – the “mere measurement effect”. Put simply, this proposes that asking someone to complete any questionnaire about a behaviour increases the likelihood that they will subsequently engage in that particular behaviour [10-12]. We will therefore attempt to control for this possible mere measurement effect by running an RCT with 3 arms, (1) no questionnaire, (2) general health belief questionnaire and (3) general health belief questionnaire with two additional AR questions. This will allow us to test whether AR leads to a significant increase in FOBT screening uptake, over and above the mere measurement effect. In RCT arm 2, participants will be asked to complete a questionnaire assessing general beliefs about health (but critically not AR). The health belief scale we will employ is the Multidimensional Health Locus of Control Scale [13]. This scale measures the individual’s belief that health (and health outcomes) are determined primarily by: (a) themselves (internal) (b) chance or fate and (c) powerful others (e.g. doctors). Importantly, individuals who believe their health outcomes are largely predetermined by fate (e.g. high chance locus of control) are significantly less likely to engage in health protective strategies, such as FOBT screening [14].

#### ***Emotional barriers to FOBT***

Finally, a key potential psychological barrier to collecting and returning one’s own stool sample is the emotion of disgust. Jones at al. [15] recently assessed patient-reported barriers to CRC screening in over 6,000 participants. In relation to FOBT screening, they found that two major perceived barriers were commonly reported: “I do not want to handle my stool” and “I do not want to keep my stools on a card in my house”. Furthermore, Chapple et al. [16] conducted a qualitative study on barriers to FOBT, and found that many participants reported disgust at the idea of handling stools, together with concern about posting their samples in the mail. Accordingly, we will also test whether those individuals who report higher levels of disgust (the so-called “ick factor”) [17], are significantly less likely to return their FOBT sample.

### Relevant evidence from the CRC screening literature

Recently, Gregory et al. [18] concluded that: “Beliefs about the benefits of screening and the barriers to completing CRC screening are key predictors of participation, and provide a focus for intervention programs”. It is important to note, however, that much of the relevant CRC screening literature is focused on the much more invasive flexible sigmoidoscopy (FS), rather than our specific focus, FOBT.

Wardle et al. [19] conducted an intervention trial comparing a psycho-educational booklet versus control in a trial aimed at increasing participation in FS screening in the UK. Importantly, the development of their intervention booklet was influenced by regret theories. Resultant FS screening attendance was significantly higher in the intervention group (53.5%) versus the control (49.9%). Power at al. [20] subsequently found that AR was better at predicting intention to attend, rather than actual attendance for FS. This finding is at variance with the large body of evidence which has shown that when people anticipate regret if they contemplate failing to carry out a behaviour, they are more likely to act on their intentions [9]. However, attending for FS is also clearly a bigger resource requirement than returning a FOBT screening test by post. Power et al. [20] concluded that despite AR predicting intention, social factors such as low SES and difficult lives may play an important role in acting as barriers to implementing intentions.

#### ***Social Inequalities in FOBT uptake***

Whitaker et al. [21] extended this work by studying the relationship between low SES, social cognitive variables and FS screening attendance. They focused on the construct of “consideration of future consequences” (CFC), a construct that has clear similarities to AR. An example of a questionnaire item tapping CFC is “I’m prepared to make sacrifices now to benefit in the long run”. Both CFC and AR are examples of temporal self-regulation models [22]; both include consideration of the future (anticipation) and a strong affective component (benefits versus regrets). Whitaker et al. [21] also included a perceived benefits scale which included items that clearly tap AR, e.g. “If I don't go, I might later wish I’d been tested”. Whitaker et al. [21] found a clear SES gradient in FS attendance, and that SES differences in CFC contributed to SES differences in the perceived barriers and benefits of screening, which, in turn, contributed to differences in FS screening attendance. They proposed that interventions that take consideration of future consequences into account could promote greater socio-economic equality in screening participation. It is conceivable that high SES individuals are more trained to evaluate facts or evidence, whereas low SES participants may use emotion more to guide decision-making. Thus, our planned emotion-based AR intervention may plausibly help act to reduce SES differences in FOBT uptake.

While it may seem that our simple AR intervention (inviting participants to rate the degree of regret they may feel if they do not return their FOBT test kit) is a minor one, in a recent systematic review, Baron et al. [23] concluded that minimal cue interventions can be effective at increasing cancer screening behaviours, including FOBT. Furthermore, more intensive, tailored interventions have not proven more effective. For example, Smith et al. [24] tested a comprehensive decision aid (including booklet and DVD), which resulted in a 16% *lower rate* of FOBT completion! Thus the available evidence from the CRC screening literature to date would seem to support further rigorous evaluation of theory-based, minimal intensity interventions.

### Pilot studies

We have recently conducted a large, randomised controlled trial of the efficacy of a simple pre-notification letter embedded within the Scottish national colorectal cancer-screening programme [25]. In this study, 60,000 adults aged 50–74 years were randomly allocated to one of 3 conditions: standard invitation (no pre-notification), simple pre-notification letter posted 2 weeks before the test pack, and pre-notification letter plus a more detailed information booklet. Uptake was significantly higher with both the pre-notification letter (59.0%) and the letter plus booklet (58.5%), compared with the usual no-prior notification method of invitation (53.9%) [25]. Importantly, the increase was seen for males and females of *all* age groups and *all* deprivation categories, including the groups with the highest and lowest levels of uptake, i.e. least deprived females (letter 69.9%, usual invitation 66.6%) and most deprived males (42.6% and 36.1%). These results demonstrate that simple interventions can increase uptake in members of *all* deprivation categories [25]. However, despite this clear evidence that pre-notification significantly improved uptake, 30-64% of people sent FOBT kits plus the pre-notification letter still did not return them [25]. As the Scottish Intercollegiate Guidance Network (SIGN) have just recommended that “Population screening for colorectal cancer using the guaiac FOBT should continue in the Scottish population until further evidence on other modalities is available” [1], any increase in return rates of screening kits would help maximise the benefits of this programme.

In a different context, we have also shown that the simple AR manipulation that we propose using here led to a significant increase in intention to become an organ donor [17] and self-reported organ donor registration [26], and we are currently conducting an evaluation of the efficacy of an AR intervention on UK National Health Service Blood and Transplant verified organ donor registration [27]. The current AR intervention study in colorectal cancer screening will test whether a similar intervention significantly increases screening uptake in people from all social deprivation categories.

### Aims

We aim to test whether a simple AR manipulation, sent along with the standard FOBT pre-notification letter, will lead to a significant increase in the uptake of FOBT colorectal cancer screening in Scotland.

### Research questions

1. Does a brief, theory-based AR intervention lead to a significant increase in the uptake of FOBT colorectal cancer screening in Scotland?

2. Is the effect observed equally across genders and social deprivation levels?

3. Is the effect a general consequence of the “mere measurement effect” or is it a specific consequence of AR?

4. Is uptake influenced by participants’ health beliefs, in particular anticipated regret, disgust, intention, perceived benefit and health locus of control?

## Methods/Design

In this study we aim to manipulate AR, by asking participants to reflect on the emotional consequences of not returning their FOBT screening kit, in an attempt to increase FOBT screening uptake. We propose a simple 3-arm randomised controlled trial (RCT), (1) no questionnaire control (2) HLOC questionnaire control and (3) AR questionnaire. The CONSORT diagram is shown in Figure 1.

**Figure 1 F1:**
[figure not shown]
CONSORT diagram of study design.

### Setting

A single-centre trial based at the Scottish Bowel Screening Centre in Dundee.

### Ethical approval

Ethical approval has been granted by Tayside NHS Board, East of Scotland Research Ethics Committee (REC ref. no. 12/ES/0092).

### Recruitment

Following the method of Libby et al. [25], participants will be a randomly recruited representative sample of all participants in the national colorectal screening programme in Scotland. Participants will be sampled from all residents aged 50–74 years who have a Community Health Index Number (a unique patient identifier) that is associated with an NHS Board. As a result of the findings of Libby et al. [25], the programme now sends all eligible people a standard pre-notification letter 2 weeks before being sent a FOBT by post, which they are required to complete at home and then return to the laboratory at the Scottish Bowel Screening Centre in Dundee for analysis. Our questionnaires will be included along with this pre-notification letter.

#### ***Inclusion criteria***

All patients currently included in the Scottish Bowel Screening Programme are eligible for this study.

#### ***Exclusion criteria***

There are no exclusion criteria.

### Informed consent

Written informed consent is not being sought from participants in the current study. Participants who are allocated to the questionnaire arms will be sent an information sheet saying that we are studying the effects of attitudes towards health and bowel screening, and how they influence FOBT returns. It will be stressed that completion of the questionnaire is totally independent of the decision to return the FOBT kit, and that all responses will be anonymised and confidential. Participants in the control arm will be sent the standard pre-notification letter, as per current practice, which does not require informed consent. If we asked for informed written consent from the two questionnaire arms, we would be treating them differently from the control arm, which may confound any differences found between groups (as those giving informed consent may be more likely to return their screening kit), therefore invalidating the results of the study. This approach was also used in our previous study [25]. It is justified in the current study for the following reasons: 1) no harm will come to participants; 2) it would be impractical for this research to be carried out if we had to obtain informed consent from all participants, as the control arm are receiving no intervention; 3) the data we are seeking to use (i.e. regarding return of FOBT kits) is already available to screening staff at the Scottish Bowel Screening Centre and will be completely anonymised before merger with the questionnaire data; and 4) the potential benefits to participants outweigh the costs. We obtained full UK NHS IRAS ethical approval for this approach (Tayside NHS Board, East of Scotland Research Ethics Committee; REC ref. no. 12/ES/0092).

### Design

We will adopt a simple, between-groups, three-arm (no questionnaire control, HLOC control questionnaire or AR questionnaire), prospective RCT design, following Libby et al. [25]. A large, nationally representative, random sample of the Scottish general public who are invited to participate in the national screening programme will be sampled via post. Participants who are allocated to the questionnaire arms will be told that we are studying the effects of attitudes towards screening.

#### ***Control***

Participants in the control arm will be sent the standard pre-notification letter, according to current practice.

#### ***HLOC Intervention***

Those randomly allocated to the HLOC group will also be sent the pre-notification letter plus the 18-item HLOC scale [13]. HLOC participants will also be asked to rate their perceived disgust (ick factor) and perceived benefit of returning their FOBT using modified versions of the ick-factor scale and perceived benefit scales from O’Carroll et al. [17], as well as rating their intention of returning the FOBT test, all using simple 1–7 Likert-type scales. Participants will be asked to return this brief questionnaire in a stamped addressed envelope that will be provided. We predict that high scores on chance HLOC will predict lower return rates, as this taps a fatalistic view of health and health outcomes.

#### ***AR Intervention***

Those allocated to the AR group will also be sent the pre-notification letter and will be asked to complete the same HLOC/ick/perceived benefit questionnaire as the HLOC group with 2 additional AR questions. Following Sandberg and Conner [8], the first of these additional questions will be placed as the very first question of the survey (“If I did not complete and return my test kit I would later feel regret”) and the second will be placed immediately preceding the final question measuring intention to return the kit (“If I did not complete and return my test kit, I would later wish I had”). In order to make the two questionnaires identical in length, the HLOC questionnaire will have 2 filler questions added in the same location as the AR questions.

Social deprivation will be categorized using the Scottish Index of Multiple Deprivation (SIMD) which identifies small area concentrations of multiple deprivation across Scotland based on income level, employment, health, education, skills and training, housing, geographic access and crime. SIMD deprivation, age, and information on current and previous FOBT returns will be provided for all individuals sent the pre-notification letter, via the unique identifier, by the Information Services Division (ISD) within the National Health Service, Scotland. Hence, no personally identifiable information will be required for the purposes of this research.

### Strategies to maximise questionnaire return rate

In an attempt to ensure the highest response rate possible, we will implement, where feasible, design recommendations from recent empirical investigations on enhancing response rates in this type of field-based study. These strategies have recently been helpfully summarised in a Cochrane review [28] and include, for example: user-friendly questionnaire layout, short questionnaire, personalising the cover letter to each individual, use of coloured ink, emphasis on confidentiality, stamped (not franked) return envelopes and University Sponsorship.

### Primary outcome

Our primary outcome variable is return of the completed FOBT test kit to the central laboratory at the Scottish Bowel Screening Centre, within 6 months of the kit being sent out. Secondary outcomes will include the HLOC, AR, ‘Ick’ factor (perceived disgust), perceived benefit of completing the test kit and intention to complete the test kit. The HLOC is a well-used and validated measure which has shown good reliability.

### Analysis

Our primary analysis will be chi-square tests to explore the proportion of respondents who return the test kits within 6 months as a function of the 3 arms (control, HLOC or AR). Logistic regression will be used to examine screening uptake by treatment arm, controlling for potential between-arm differences in age, gender and social deprivation, whether a reminder letter was sent, number of previous FOBT returns, and previous failures to return. Our primary analysis will be on an ‘Analysed as Allocated’ basis, i.e. including all participants randomised to treatment arms, whether they return a questionnaire or not. Secondary analysis will be conducted on the questionnaire respondents (HLOC and AR groups only), to test the mediating role of intention, AR, health locus of control, disgust and perceived benefit in influencing FOBT returns.

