### Power calculations

Following Libby et al. [25], a sample of 60,000 subjects (20,000 randomized to the usual pre-notification letter group, 20,000 randomized to the HLOC Group and 20,000 to AR group) would enable an increase in FOBT uptake of between 3% and 5% to be detected in all social deprivation groups with 80% power at the 5% level.

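### The primary test is a valid but unadjusted chi-square, although screening history is supplied for everyone sent the letter; a baseline-adjusted primary estimate would gain precision at almost no cost

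*Protocol article*

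**What the plan says.** The Analysis section sets the primary test: "Our primary analysis will be chi-square tests to explore the proportion of respondents who return the test kits within 6 months". It compares the three arms with no covariates. Later in the same section the primary analysis set is defined as everyone randomised, regardless of questionnaire return.

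The next sentence adds a model: "Logistic regression will be used to examine screening uptake by treatment arm, controlling for potential between-arm differences in age, gender and social deprivation". Its covariate list continues with "whether a reminder letter was sent, number of previous FOBT returns, and previous failures to return". The text does not say whether this model is primary or secondary. The only reason given for it is possible differences between arms.

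On data availability, the Sampling and randomisation section says: "SIMD deprivation, age, and information on current and previous FOBT returns will be provided for all individuals sent the pre-notification letter". That covers all three arms. Gender and previous failures are not named in that sentence, but the Analysis section plans to use both.

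The Power calculations section plans for an "increase in FOBT uptake of between 3% and 5% to be detected in all social deprivation groups", "with 80% power at the 5% level", with "20,000 randomized to the HLOC Group and 20,000 to AR group". It gives no separate target for AR against HLOC.

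**The concern.** With 20,000 people per arm allocated by computer, chance imbalance between arms is negligible, so correcting imbalance is a weak reason to adjust. The useful reason is that baseline variables which predict kit return remove outcome variance and so narrow the interval for the arm effect. The plan does not use that argument and gives the label 'primary' to the test that leaves the variance in.

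The contrast where this could matter is AR against HLOC. Research question 3 asks whether any effect is specific to anticipated regret, and the two questionnaires differ only in two items. The cervical screening study cited in the Background, which used a similar three-group design, found 26% and 26% attendance by intention to treat in the two questionnaire groups. If the true difference is about one point, precision affects what a non-significant result can say. Precision also matters within deprivation groups, where the plan's own power is close to its limit.

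**Working it through.** **Inputs from the protocol.** 20,000 per arm; 80% power; 5% level; 59.0% uptake with the pre-notification letter, with 42.6% (most deprived males) and 69.9% (least deprived females) as extremes (Pilot studies section).

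**Assumptions.** Two-sided test; five equal deprivation groups (the number is not stated), so 4,000 per arm per group, or 2,000 when also split by sex; R-squared for baseline covariates, ranged because the protocol gives none.

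**The plan's figure.** Solving the two-proportion power formula for the difference detectable at 80% power gives 2.8 to 3.1 points at 4,000 per arm and 4.0 to 4.4 points at 2,000 per arm, over baselines of 42.6% to 69.9%. The stated 3–5% is therefore consistent with an unadjusted comparison within deprivation groups.

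**Unadjusted AR v HLOC, whole trial.** For 59% v 60%:

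- SE = sqrt(2 × 0.595 × 0.405 / 20,000) = 0.49 points.
- Power = Φ(1.00/0.491 − 1.96) = Φ(0.08) = 53%.
- Detectable difference at 80% power = (1.96 + 0.84) × 0.49 = 1.37 points.
- 95% CI half-width = 1.96 × 0.49 = 0.96 points.

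**Effect of adjustment.** Explaining a share R² of outcome variance multiplies the SE by sqrt(1 − R²), equivalent to a sample of n/(1 − R²). Baseline uptake is 59%.

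| R² | Equivalent sample | Power, 1 point, 20,000/arm | Detectable difference, 20,000/arm | Power, 3 points, 4,000/arm |
|---|---|---|---|---|
| 0 | 1.00 | 53% | 1.37 | 78% |
| 0.03 | 1.03 | 54% | 1.35 | 80% |
| 0.05 | 1.05 | 55% | 1.34 | 80% |
| 0.10 | 1.11 | 57% | 1.30 | 82% |
| 0.20 | 1.25 | 62% | 1.23 | 87% |
| 0.30 | 1.43 | 68% | 1.15 | 91% |
| 0.40 | 1.67 | 75% | 1.07 | 94% |

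For a 3-point difference in the whole trial, power exceeds 99.9% in every row.

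**What R² might be.**

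- *Sex and deprivation alone.* The Abstract gives 39% to 67%. Spread evenly over that range, the variance is 0.28²/12 = 0.0065. Divided by 0.59 × 0.41 = 0.242, this gives R² of about 0.03. Even half the sample at each extreme gives only 0.14²/(0.53 × 0.47) = 0.08.
- *Screening history.* For a share π of past returners with return rates a (past returners) and b (others), and overall rate p, R² = π(1 − π)(a − b)²/[p(1 − p)]. Assumed values π = 0.55, a = 0.75, b = 0.40 give 0.13; π = 0.50, a = 0.90, b = 0.28 give 0.40. None of these rates is in the protocol.

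**Simulation check.** A test stratified by an assumed three-level history was compared with the crude test, 600 runs per scenario. At R² of about 0.33 and a true difference of about 1.0 point, power went from 53% to 67%. At R² of about 0.14 and about 1.2 points, it went from 69% to 75%. Type I error was 4–5% for both tests.

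**Why the listed model should not simply be promoted.** Suppose reminders go to people who have not yet returned a kit, 75% of eventual returns arrive before that, and final uptake is 59% v 60% (assumptions). Among those reminded, uptake is 0.1475/0.5575 = 26.5% v 0.15/0.55 = 27.3%, a difference of 0.8 points. Among those not reminded, everyone returned, so the difference is zero. Conditioning on the reminder would hide part of the effect.

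**The case against.** The strongest reply is that nothing is wrong. Under simple 1:1:1 randomisation with everyone analysed as allocated, the unadjusted chi-square is valid. That stands.

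Second, the adjusted model is already planned, and the Timetable names logistic regression as the work of months 15–18, with the analytic strategy to be finalised in months 8–14. A reader might infer that screening history goes unused or that the conclusion must rest on the chi-square alone. The protocol does not support the first, and the second is an inference. What remains is that the chi-square carries the primary label, and the planned model, with its reminder term, is not a suitable replacement as listed.

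Third, a reader might infer that the plan expects a small AR-v-HLOC effect. It does not say so. Its only target is 3 to 5 points within deprivation groups, and 26% v 26% comes from one study in another screening programme. With an unadjusted half-width of 0.96 points, a null result would already exclude 3 points overall. It is therefore too strong to say that adjustment decides whether a null is informative.

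Fourth, the gain rests on assumed R². The only prognostic figures in the protocol, by sex and deprivation, support about 0.03, which is worth one percentage point of power. People newly invited have no history, which weakens the covariate for them. Both points stand and limit the claim.

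Finally, the word 'respondents' in the primary-analysis sentence might be read as restricting the test to people who returned a questionnaire. The same section rules that out.

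**Conclusion.** The point stands as an efficiency improvement, not as an error or a source of bias. The primary test leaves out baseline information that will be held for all arms, and the planned model does not already supply a suitable adjusted primary estimate.

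The gain may be trivial or useful. For a true 1-point AR-v-HLOC difference, power rises from 53% to 54–55% if R² is 0.03–0.05, and to 75% if it is 0.40. The detectable difference falls from about 1.4 points to 1.07 at best. At the plan's own 3 points there is nothing to gain overall. Within a deprivation fifth, power moves from about 78% to 80–91% at R² 0.05–0.30.

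These figures rest on a two-sided 5% test, 59% uptake, five equal deprivation groups and an assumed R². That the reminder is post-randomisation is also an assumption, because the protocol does not say when reminders are sent.

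**What to change.** In the Analysis section, name as primary, for each arm contrast, a logistic regression in all randomised participants. Adjust for baseline variables only: age, gender, SIMD, number of previous returns and previous failures, with a separate category for people with no previous invitation. Leave the reminder-letter term out of this model. Report a standardised (marginal) risk difference with 95% CI, and keep the chi-square as a supportive analysis. State precision as the reason for adjusting, in place of differences between arms.

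The cost is small. No new data source is needed beyond what the plan already intends to use. The covariate set changes slightly, and the standardised risk difference is a minor extra analysis step.
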